### Allocation of switch moment

Follow-up care will be provided according to the current follow-up condition of the participating centre. For three of the six participating centres, this switch to including patients under condition B will occur after six months of including patients under condition A. For the other three participating centres, the switch to condition B will occur after 12 months of including patients under condition A.

The moment of switching will be allocated using a simple randomisation based on a single sequence. The randomisation will be performed between the six participating centres before the start of inclusion by the study coordinator and the project leader.

### Blinding

Due to the study design, blinding is not possible.

### Data collection methods

Data from PLCRC, the Netherlands Comprehensive Cancer Organzsation (IKNL) and data from electronic patient files will be merged before data analysis. These data from the electronic patient files can be gathered due to the informed consent of patients for PLCRC. During the DISTANCE-trial, these data will be stored in an electronic case report form using the Castor Electronic Data Capture system. The data from the electronic patient files will be locally collected in the participating centres by the study coordinator. The likelihood of loss to follow-up is very low due to the nature of the study design, as patients will likely receive follow-up in the participating centre for the remainder of their follow-up trajectory.

### Data management

All data from PLCRC and IKNL are coded with a study number. These study numbers will be linked to the data extracted from the electronic patient files and will be stored in a pseudonymised manner. As far as possible, international ontologies and classifications will be used to code the data.

During the trial, only members of the research team have access to the data collected for this study. The metadata and raw dataset of the DISTANCE-trial will be made findable for subsequent research through the DANS EASY repository using the Radboud university medical center’s Research Information System (RIS) once the study has ended. The data will be accessible upon reasonable request. DANS EASY assigns a digital object identifier (DOI) code to the archived dataset. This DOI code will be added to the registration in RIS.

All data, software codes, research materials, published or unpublished will be managed and securely stored for a period of 15 years. The raw dataset will be stored in a comma-separated values format. This storage will be performed in accordance with guidelines from the Association of Universities in The Netherlands (VNSU) in the digital research environment of the Radboud university medical center.

### Statistical methods

#### Primary outcome

Analysis of the primary outcome will consist of mixed model analysis. In this mixed model analysis, a random effect will be used for each hospital to account for the similarity of patients within a hospital. Fixed effects will be used for follow-up condition and recruitment period.

As the primary outcome of interest is a difference in proportions on hospital level, a linear mixed model will be used (identity link).

Fit of the model on the hospital and recruitment period averages will be assessed using residual plots and observed versus predicted plots. If the fit is not considered acceptable, improvement of fit will be sought using a generalised mixed model and varying the following choices:Difference in proportion (identity link), odds ratio (logistic link) or ratio (log link);Error distribution (normal distribution, binomial distribution or Poisson);Adjustment for hospital level characteristics (e.g., academic, teaching, community), patient and tumour level characteristics.

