#### Secondary outcomes

The secondary outcomes resulting from questionnaire data will be measured at 12 months after curative surgical resection (baseline), 18 months (6 months after inclusion) and 24 months (12 months after inclusion, end of study). The following secondary outcomes result from questionnaire data:HRQoL, measured by the European Organisation for Research and Treatment of Cancer Quality of Life (EORTC QLQ-C30) Questionnaire;Fear of cancer recurrence, measured by the Cancer Worry Scale (CWS) questionnaire;Anxiety, depression and distress, measured by the Hospital Anxiety and Depression Scale (HADS) questionnaire;Utility measure, measured by the EuroQol 5-Dimension 5-Level (EQ-5D-5L) questionnaire;Extramural costs, measured by a selection of relevant questions from the Medical Consumption Questionnaire (iMCQ) from the institute of Medical Technology Assessment;Productivity losses, measured by the Work Ability Index (WAI) questionnaire.

The following secondary outcomes result from other data than questionnaire data, and will be measured over the total study period:Cost-effectiveness, evaluated by integration of the questionnaire data and data extracted from the electronic patient records;OS, evaluated by data on vital status from the NCR; andCancer-specific survival, evaluated by data from the NCR on vital status and electronic patient records.

All abovementioned parameters will be compared between patients included under condition A and condition B.

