#### Secondary outcomes

As the PROMs are (semi-)continuous, their analysis will consist of a linear mixed model analysis. This mixed model analysis will have a random effect for each hospital, to account for the similarity of patients within a hospital. It will also have a random effect for patients within each hospital, to account for repeated measures within a patient. Fixed effects will be included in the analysis for follow-up condition, recruitment period, patient characteristics and tumour characteristics [14]. Model fit will be assessed similarly.

The EQ-5D-5L will be used to measure quality adjusted life-years (QALYs). The scores will be transformed into health utilities using the Dutch tariff [22]. The cost-effectiveness evaluation will be carried out according to the Dutch handbook for health-economic evaluations [23]. Analysis will be conducted in agreement with the intention-to-treat principle, from a societal perspective. The time horizon will be 12 months.

Healthcare costs, out-of-pocket costs of the patient and cost in the other sectors will be included (e.g., productivity losses). Hospital resource use will be taken from the hospital records, and will include all diagnostic testing, hospital visits, telephone and email consultations. Medical resource use outside the hospital, as measured using an adapted version of the iMCQ, will provide information on visits to the GP or use of paramedical care. The WAI will provide information on productivity losses due to follow-up visits. The cost associated with resource use will be derived from the Dutch handbook for costing, and tariffs and prices published by the Dutch Healthcare Authority [24]. Total costs will be calculated by multiplying resource use by integral cost prices.

As the time horizon is 12 months, neither costs nor effects need to be discounted. Incremental costs per QALY – the incremental cost-utility ratio (ICUR) – will be calculated with their 95% confidence intervals using 5,000 bootstrap replications, which will be projected on a cost-utility plane. In addition, ICUR acceptability curves will be presented and sensitivity analysis will be performed focusing on uncertainty surrounding most important cost items. To correct for potential baseline differences in patient population between the current care and the intervention group, covariate adjustment of the cost and QALY difference will be carried out.

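### The default primary model leaves out patient and tumour characteristics and admits them only on poor fit, although the PROM and cost analyses adjust from the start

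*Protocol article*

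**What the plan says.** Under Statistical methods, Primary outcome, the default is a linear mixed model with identity link, in which "a random effect will be used for each hospital to account for the similarity of patients within a hospital". The fixed part is closed: "Fixed effects will be used for follow-up condition and recruitment period". Fit is then judged on hospital and recruitment-period averages. "If the fit is not considered acceptable, improvement of fit will be sought using a generalised mixed model", and one of the choices that may then be varied is "Adjustment for hospital level characteristics (e.g., academic, teaching, community), patient and tumour level characteristics".

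Under Statistical methods, Secondary outcomes, the PROM models are different from the outset: "Fixed effects will be included in the analysis for follow-up condition, recruitment period, patient characteristics and tumour characteristics". No reason is given there. For the cost and QALY differences a reason is given: "To correct for potential baseline differences in patient population between the current care and the intervention group, covariate adjustment" is planned.

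Other sections bear on how patients enter. Hospitals are randomised before inclusion starts (Allocation of switch moment). There is no blinding (Blinding). Only PLCRC participants are analysed, and a patient can still join PLCRC at the 12-month clinic visit (Interventions; Recruitment). Age, sex, tumour site, TNM class, systemic or radiation treatment and comorbidity count are all recorded (Other variables).

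**The concern.** The article accepts that patients under A and B may differ at baseline and acts on this for costs and QALYs, but not by default for its primary contrast. The trigger it sets for adjusting that contrast is poor fit, which does not measure case-mix imbalance.

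Two routes could make case mix follow condition inside one hospital. First, late consent to PLCRC can be sought at the same visit at which home-based follow-up is explained under B. Second, the exclusion of patients who need longer in-hospital follow-up is a staff judgement. It may be applied more readily when inclusion means leaving in-hospital care. If patients likely to need more contact are thereby rarer under B, the unadjusted difference is too favourable to PHFU. If they are commoner, it is too unfavourable. What is at stake is the size of the reported reduction in contact.

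**Working it through.** **1. The plan's own figures.** From Sample size: 6 hospitals, 20 patients per hospital per six months, 360 in total, so 360 / (6 × 20) = 3 periods. Condition A fills 3 × 1 + 3 × 2 = 9 hospital-periods, and 9 × 20 = 180. Condition B fills the other 9, also 180. Both totals reproduce.

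Power uses the Hussey-Hughes variance (random hospital intercept, fixed period and condition), ICC 0.20, a 40-point difference, two-sided alpha 0.05 (assumed, as none is stated) and power = Φ(0.40 / SE − 1.96):
- 100% v 60%: SE 0.076, power 99.9%
- 70% v 30%: SE 0.101, power 97.7%
- maximum variance 0.25: SE 0.110, power 95.3%

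The claim of at least 80% holds under that model. It does not depend on covariates, so this point changes no stated number.

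**2. Why hospital and period terms, and the fit check, miss it.** Let factor k be δ_k more or less common under B and move contact under B by γ_k. With contact near 100% under A, it has no room to act there. The expected hospital-period mean is

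hospital_i + period_j + X_ij (θ + Σ δ_k γ_k), with X_ij = 1 under B.

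The shift has the same pattern as condition, so the condition coefficient estimates θ + Σ δ_k γ_k. The residuals of the averages are the same as with no shift, so residual and observed-versus-predicted plots on averages can look perfect. If all δ_k = 0, the coefficient is θ and there is no bias.

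**3. Size.** The article gives no δ or γ, so these are assumptions. For two equal factors, bias = 2 × δ × γ. The simulation used 1,500 trials per setting, 6 × 3 × 20 patients, A 100%, B 40%, hospital SD 8 points under B, and factors rarer under B:

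| δ (points) | γ (points) | 2 × δ × γ | simulated bias, unadjusted |
|---|---|---|---|
| 10 | 10 | 2 | −2.1 |
| 10 | 20 | 4 | −3.9 |
| 10 | 30 | 6 | −6.0 |
| 20 | 10 | 4 | −4.3 |
| 20 | 20 | 8 | −7.9 |
| 20 | 30 | 12 | −12.0 |

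A separate run agreed within 0.3 points. For a single factor with δ from 5 to 20 and γ from 10 to 50 points, δ × γ runs from 0.5 to 10 points.

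**4. Form of the adjustment.** A common slope averages zero effect under A with γ under B, so it removes about half. In a simulation with one factor 20 points commoner under B and acting there by 40 points, the estimate was −0.569 without imbalance, −0.484 unadjusted and −0.529 with a main effect. That removes 4.5 of 8.5 points. Letting the factors act by condition brought the bias within 0.4 points. The SE stayed near 8 points, between 8% smaller and 5% larger.

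**5. Reference mix.** The sizes above are measured against the case mix that would hold without selection, which here is the mix under A. If the target is instead all included patients, half of them under B, the reference prevalence lies midway. The unadjusted bias is then half: 2/2 = 1 to 12/2 = 6 points. A main-effect adjustment, which removes about half, lands near that target. The reference mix therefore has to be stated.

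**The case against.** Condition plus period with a random hospital effect is an ordinary stepped-wedge model, and it matches the stated target of a difference in proportions. Randomised switch times handle stable hospital differences and common trends. The documents also limit selection: PLCRC consent is usually sought around diagnosis, patients cannot choose the condition, eligible patients enter automatically, and those who deviate are analysed by intention to treat. All of this stands. It makes selection less likely but does not exclude it, and its size is unknown.

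The simulated correction to near zero follows from adjusting for exactly the factors that were shifted. Selection on willingness or perceived need would be captured only as far as it correlates with recorded variables. This also stands. The remedy simulated had two factors, not six.

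A covariate list is often left to the analysis plan, which is not shown. But the article does not leave the matter open. It fixes the default terms and the condition for changing them, and poor fit is the wrong condition.

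Four stronger readings are tempting and are not supported:
- A reader might infer that the primary contrast is the only result left unadjusted. Survival is also compared between conditions ("OS, evaluated by data on vital status from the NCR", and cancer-specific survival likewise), and no adjustment is described for either.
- A reader might infer that the PROM models adjust because of expected baseline differences. That reason is written only for costs and QALYs.
- A reader might infer that covariates are barred from the primary model. They are named among the fallback choices.
- A reader might infer that the unadjusted estimate is biased. It is biased only if selection depends on condition.

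**Conclusion.** The point holds as a modest weakness in a stated analysis. The article foresees baseline differences between the groups, yet its default primary model does not address them, and its trigger for doing so cannot detect them.

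On assumed shifts of 10 to 20 points in two factors that each move contact under B by 10 to 30 points, the bias is about 2 to 12 points relative to the mix without selection. That is 2/60 = 3% to 12/60 = 20% of the expected difference, or 2/8 = 0.25 to 12/8 = 1.5 standard errors. Even in the worst case and the unfavourable direction, 60 − 12 = 48 points remains above the 40 points used for the power statement. The direction of the result is not in question, only its size. All of this rests on condition-dependent selection on measured factors, which the documents make possible but do not show.

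**What to change.** In Statistical methods, Primary outcome, name a short fixed list from Other variables and include it whatever the fit: for example age, sex, tumour site, pathological stage, systemic or radiation treatment, and comorbidity count. Because contact under A is near 100%, either let these act by condition through centred interactions, or standardise predicted contact under A and under B to all included patients. State the reference mix, since centring at the mix under A and standardising to all included patients answer slightly different questions. Report a difference in proportions, and keep the present unadjusted model as a sensitivity analysis.

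The variables are already collected. The cost is a few lines of text, a few degrees of freedom among 360 patients and slightly more analysis work. In the two-factor simulation the SE changed by between −8% and +5%; a list of six acting by condition uses more parameters and was not simulated.

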## Methods/design

### Study setting

The study will be conducted in six hospitals in The Netherlands. The participating centres have no previous experience with PHFU for CRC. Five hospitals are non-academic teaching hospitals (Bernhoven Hospital, Catharina Hospital, Gelre Hospitals, Jeroen Bosch Hospital, Rijnstate Hospital). One hospital is a university medical centre (University Medical Center Utrecht). The six participating centres act as clusters. The study features two conditions: condition A (in-hospital, standard-of-care follow-up) and condition B (PHFU). All six participating centres will start including patients in condition A. Three centres will perform the switch from condition A to condition B after six months of participation; the other three centres will perform the switch from condition A to condition B after 12 months of participation. The switch will be performed without a transition period. A graphical overview of the study design and setting is depicted in Fig. 1.

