### Sample size

In this SW-CRT, it is expected that the primary endpoint, the proportion of patients who had contact with the hospital regarding CRC follow-up care within the 12 months follow-up period, is approximately 100% in the in-hospital, standard of care follow-up and approximately 40% during the PHFU.

Over a realistic range of assumptions, this design has at least 80% power to detect a meaningful difference in the proportions of patients contacting the hospital. Specifically, this is the case:If at least 20 patients per six months per hospital can be included in the DISTANCE trial;If the hospital intra cluster coefficient (ICC) of the primary outcome is no more than 0.20 (typical hospital ICC are around 0.05–0.10) [12]; andIf the difference between the primary outcome in condition A and condition B is more than 40% (expected difference based on implementation in Radboud university medical center: 70%).

Of note, if 20 patients per hospital per half year will be included, then the total number of patients will be 360. Of these 360 patients, 180 will be included under condition A and 180 will be included under condition B.

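### The primary effect measure, error distribution and covariates may be re-chosen after fit plots are seen, with no criterion or order; if contact in condition A is exactly 100%, the odds-ratio option has no finite estimate

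*Protocol article*

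**What the plan says.** Under Statistical methods, Primary outcome, the protocol article sets a default: a linear mixed model with identity link, a random effect for hospital, and fixed effects for follow-up condition and recruitment period. The reason given is that the quantity of interest is a difference in proportions.

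Fit is judged from residual plots and observed-versus-predicted plots of the hospital-by-period averages. The section then continues: "If the fit is not considered acceptable, improvement of fit will be sought using a generalised mixed model and varying the following choices". The first listed choice is the effect measure: "Difference in proportion (identity link), odds ratio (logistic link) or ratio (log link". The second is the error distribution (normal, binomial or Poisson). The third is adjustment for hospital, patient and tumour characteristics, with examples of hospital type only.

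The Sample size section expects that the primary endpoint "is approximately 100% in the in-hospital, standard of care follow-up and approximately 40% during the PHFU". The Blinding section says that blinding is not possible.

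**The concern.** The link in this list is more than a technical setting. Moving from identity to logit or log changes the quantity reported from a difference to an odds ratio or a ratio. The plan allows that move on a visual judgement of plots built from the outcome by hospital and period, in an unblinded trial. No criterion says when fit is unacceptable, which alternative comes first, or whether the difference must still be reported as primary.

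The planning rates make this more than a formality. A proportion at or near 1 in one condition is where a constant-variance linear model looks worst on the prescribed plots, and also where the logistic alternative can fail. At stake is which effect measure the trial reports, and whether that choice is independent of the result.

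**Working it through.** **1. The plan's own figures.** "if 20 patients per hospital per half year will be included, then the total number of patients will be 360": 20 × 6 hospitals × 3 periods = 360. Condition A occupies 6 + 3 + 0 = 9 hospital-periods, so 9 × 20 = 180 per condition. The size reproduces.

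For power, the article claims that "this design has at least 80% power to detect a meaningful difference in the proportions of patients contacting the hospital", for a difference above 40 points and an ICC that "is no more than 0.20 (typical hospital ICC are around 0.05–0.10"). The stepped-wedge variance with fixed periods and a random hospital intercept is

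Var = Iσ²(σ² + Tτ²) / [(IU − W)σ² + (U² + ITU − TW − IV)τ²],

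with I = 6, T = 3, U = 9, W = 0 + 9 + 36 = 45 and V = 3×4 + 3×1 = 15, so the bracket is 9σ² + 18τ². I assume two-sided alpha 0.05 (the article gives none) and the largest possible total variance, 0.25.
- ICC 0.05: σ² = 0.2375/20 = 0.011875, τ² = 0.0125, SE = 0.103, 0.40/0.103 = 3.89, power 97%.
- ICC 0.20: σ² = 0.20/20 = 0.010, τ² = 0.05, SE = 0.098, 0.40/0.098 = 4.06, power 98%.

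The claim of at least 80% holds under the stated model.

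**2. What the fit plots would tend to show.** Patient-level variance p(1 − p) is 1.0 × 0 = 0 in A and 0.4 × 0.6 = 0.24 in B. The plan looks at hospital-period averages, so the stated model was simulated: 500 trials per scenario, B rate 0.40, hospital rates varying in B by a beta distribution, REML fit.

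| True A rate | ICC | Any fitted mean > 1 | Any fitted mean > 1.05 | RMS residual A / B |
|---|---|---|---|---|
| 1.00 | 0.05 | 100% | 44% | 0.030 / 0.098 |
| 1.00 | 0.10 | 100% | 69% | 0.048 / 0.104 |
| 1.00 | 0.20 | 100% | 90% | 0.079 / 0.121 |
| 0.95 | 0.05 | 47% | 16% | 0.048 / 0.100 |
| 0.95 | 0.20 | 91% | 68% | 0.084 / 0.122 |

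The mechanism is simple. A hospital with an above-average B rate receives a positive intercept, which also lifts its fitted A mean past 1.

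**3. Whether the alternatives can be estimated.** Only period 2 contains both conditions: 60 patients in A and 60 in B. Suppose all 60 A patients in period 2 have contact. In the logistic model, add k to the period-2 and period-3 effects and subtract k from the condition effect. Every fitted probability stays the same except that for A in period 2, which moves towards 1. The likelihood therefore rises without limit, and a random hospital intercept does not prevent it. With independent patients at a common A rate p, the probability of this is p^60:
- p = 1.00: 100%
- 0.99: 0.99^60 = 55%
- 0.97: 16%
- 0.95: 5%

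In one data set with A at 100%, fitted without the hospital effect, the logit coefficient ran from −11.8 to −26.8 to −37.8 at 10, 25 and 100 iterations. The Poisson log-link coefficient was stable at −0.836 (SE 0.235), a ratio of 0.433. The Poisson ratio was finite in 500 of 500 trials in every scenario. Binomial models with identity or log link have a finite difference or ratio but sit on the boundary p = 1 and may not converge.

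**4. How much the choice of measure matters.** With B at 0.40:
- A = 0.95: difference −0.55, ratio 0.42, odds ratio (0.4/0.6)/(0.95/0.05) = 0.035.
- A = 0.99: difference −0.59, ratio 0.40, odds ratio (0.4/0.6)/(0.99/0.01) = 0.0067.

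Four points in A change the odds ratio fivefold and the difference by 0.04.

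**5. Which part of the linear model needs repair.** At A = 100% the mean estimated difference was −0.600 to −0.609 against a true −0.60. The mean model SE was 0.068 to 0.069, against an empirical SD of 0.085 to 0.116. The estimate is sound and its standard error is too small in this scenario.

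**The case against.** Checking fit before inference is ordinary practice, a default model is named, and thresholds, fallback order and covariate lists usually belong in an analysis plan, which is not shown. That excuses missing detail. It does not excuse what the article states: that the effect measure itself is one of the things to be varied.

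Four stronger readings are tempting, and the documents do not support them.
- A reader might infer that the switch is almost certain. No probability can be attached to a trigger without a criterion. The Sample size section says approximately 100%, and the warning signs become less frequent at 95% to 99%.
- A reader might infer that all the alternatives fail. Only the logistic link has no finite estimate. The Poisson variance misfit in A concerns standard errors, not estimability.
- A reader might infer that error control is lost. No type I error rate was computed, and nine link-by-distribution combinations is only an upper bound. With power of about 97% or more for 40 points and a planned difference of 100 − 40 = 60 points, a reversed conclusion is not demonstrated.
- A reader might infer that adjusting for hospital type breaks the model because "One hospital is a university medical centre". Condition varies within every hospital, so that indicator can be estimated and does no harm to the within-hospital contrast.

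**Conclusion.** The point stands in a limited form. The plan names the difference in proportions as its target and then permits that target, the error distribution and the covariates to be replaced after outcome-based plots are seen, with no criterion or order. At the planned rates the linear model tends to show the features that could prompt a switch. One of the permitted destinations, the odds ratio, has no finite estimate if A is exactly 100%, and is fragile just below it.

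The harm shown is to the definition of the primary result, not to power or to the direction of the conclusion. The change should be made. The figures rest on 20 patients per hospital-period, a B rate of 0.40, independent patients at a common A rate, and hospital variation placed in B only.

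**What to change.** State that the risk difference between conditions, adjusted for recruitment period, is the sole primary effect measure whatever the model fit. Delete the choice of link, error distribution and covariates from the primary analysis.

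If fit is poor, keep the identity-link estimate and change only its standard error, for example to a cluster-robust standard error with a small-sample correction for six hospitals. The performance of that correction in this design was not simulated and should be checked before it is fixed. Do not use a condition-specific residual variance. When every A outcome is 1 that variance goes to zero: on one simulated data set the REML criterion rose from 246 to 1,680 as the A variance fell from 0.1 to 1e-8, with no maximum.

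Report a penalised logistic model standardised to a risk difference, the Poisson ratio, and covariate-adjusted models as labelled sensitivity analyses.

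The cost is a wording change, less analyst flexibility and possibly a wider interval. In the simulated scenario with A at 100%, replacing the model SE by the empirical SD moves the half-width from 1.96 × 0.068 = 0.13 to between 1.96 × 0.085 = 0.17 and 1.96 × 0.116 = 0.23, before any small-sample correction. The planned effect is 0.60.
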